HXZQ is composed of Herba Pogostemonis (Huoxiang), Pericarpium Arecae (Dafupi), Perillae (Zisu), Rhizoma Pinelliae (Banxia), Pericarpium Citri Reticulatae (Chenpi), Cortex Magnoliae Officinalis (Houpo), Radix Angelicae Dahuricae (Baizhi), Poria (Fuling), Rhizoma Atractylodis Macrocephalae (Baizhu), Radix Platycodonis (Jiegeng), and Radix Glycyrrhizae (Gancao). Experiments have revealed that it could resolve dampness pattern in rat models through multiple approaches: normalizing gastrointestinal dysfunction [17], improving immune and metabolic functions [18], and regulating gut microbiota disturbance [19]. Currently, HXZQ is an over-the-counter (OTC) medication and has various dosage forms such as oral liquids, capsules, and pills [20]. Despite its rich history of human use, HXZQ still requires high-quality evidence of postmarketing evaluation when used as a Chinese patent medicine. In addition, it also lacks accurate clinical positioning based on CM patterns.

Hence, we utilize a master protocol comprising two randomized controlled trials (RCTs) and a real-world observational study to evaluate HXZQ oral liquid for dampness pattern in AD and IBS-D, respectively, with the aim of identifying the accurate pattern-defined population of HXZQ. Master protocol is defined as a single overarching protocol designed with multiple substudies [21]. It allows the research questions to be addressed in an efficient way by minimizing time and infrastructure costs as compared with conducting separate studies [22]. Meanwhile, this study is actually developed under the pattern dominating different diseases research model (Yi Zheng Tong Bing model), which takes CM pattern as the target of intervention and focusses on the correlation between CM patterns and disease outcomes [23, 24]. Thus, the resulting procedures of our research will also provide a reference for future studies.

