#### 2.4.2. Concomitant Medications

For AD patients in the RCT, topical daily use of moisturizers such as urea ointment is recommended and permitted. Cetirizine hydrochloride tablets will be used in case of intolerable itching, and the dosage and frequency should be recorded. Other effective medications (orally or externally) and phototherapy for AD are not allowed. For IBS-D patients enrolled in the RCT, intolerable abdominal pain or diarrhea can be treated with emergency medications prescribed by the clinician. The name and dosage of the medication should be recorded in the patient's diary. Besides, any other medications and CM physiotherapy (such as acupuncture, moxibustion, or cupping) that may be effective for IBS-D, or can relieve abdominal pain and diarrhea, are prohibited. Treatments in the observational study will be provided by clinicians according to patients' specific conditions, and medical records of each patient should be exactly documented.

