#### 2.4.3. Randomization and Blinding

Eligible patients in each RCT will be equally randomized to receive either HXZQ oral liquid or placebo through an interactive web response system. A center-stratified random sequence will be created with SAS 9.2 (SAS Institute Inc., Cary, USA). The randomization will be independently performed and managed by the Institute of Basic Research in Clinical Medicine (IBRCM), China Academy of Chinese Medical Sciences (Beijing, China). Patients and researchers involved in the trial including clinicians, research assistants, outcome assessors, and statisticians will be blinded to treatment allocation. In the observational study part, patients will receive no experimental interventions of this study. Investigators will just document the medical records, and blinding is not required.

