Finally, an overall analysis will be performed combining multiple subgroups to comprehensively investigate the effect of HXZQ for dampness pattern. These subgroups analyses will include (1) HXZQ vs. placebo for AD patients, (2) HXZQ vs. placebo for IBS-D patients, (3) AD patients with dampness pattern vs. AD patients without dampness pattern, (4) IBS-D patients with dampness pattern vs. IBS-D patients without dampness pattern, and (5) patients with dampness pattern vs. patients without dampness pattern. We will pay special attention to the analysis of CM pattern, including the clinical manifestations, tongue and pulse signs, and pattern diagnosis. Based on the time sequence of clinical symptoms and CM pattern transition at each visit, a Markov model will be constructed to describe the changes of CM pattern over time [36]. The influence of interventions and related covariates (gender, age, disease, condition, CM pattern, etc.) on this change process will also be detected using mixed-effects models, or multilevel models. Then, to identify whether there are common or disease-specific changes of dampness pattern in different diseases, we will compare the dampness pattern changes of AD and IBS-D patients. Furthermore, the correlation of CM pattern and disease outcomes will be analyzed. Several methods such as logistic regression model, Cox regression model, and Bayesian hierarchical model will be explored and compared to establish a reasonable and accurate disease prognosis predictive model based on CM pattern [35].

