## Figures and Tables

**Figure 1 fig1:**
[figure not shown]
Study flowchart. AD, atopic dermatitis; IBS-D, diarrhea-predominant irritable bowel syndrome; HXZQ, Huoxiang Zhengqi oral liquid.

**Table 1 tab1:** Summary of study populations and intervention.

Trial name	Study design	Population	Intervention	Sample size
CHARM	RCT	AD with dampness pattern	HXZQ oral liquid vs. placebo	218
CHAIRS	RCT	IBS-D with dampness pattern	HXZQ oral liquid vs. placebo	212
—	Observational study	AD with nondampness pattern	—	460
		IBS-D with nondampness pattern		110

**Table 2 tab2:** Inclusion and exclusion criteria for patient selection in the RCTs.

Inclusion criteria	Exclusion criteria
Patients who meet all of the following criteria are eligible for the RCTs:	Patients who meet any of the following criteria are not eligible to participate in the RCTs:
1. Patients between 18 and 70 years of age and informed consent obtained	1. Patients with any uncontrolled cardiovascular, respiratory, digestive, urinary, or hematological disease; known cancer or mental illness
2. Diagnosed with CM dampness pattern	2. Examination results show ALT or AST levels exceeding 2 times the upper limit normal value; or BUN level exceeds 1.5 times the upper limit normal value during the screening period
3. CHARM (a) 1% < body surface area (BSA) < 10% (b) 1 ≤ investigator's global assessment (IGA) ≤ 3	3. Anyone allergic to any medicine or ingredients used in the study
	4. Women who are pregnant or lactating or plan to become pregnant in three months
4. CHAIRS (a) Initial irritable bowel syndromes symptom severity (IBS-SSS) score >75 (b) Patients had to be literate	5. Those who are considered unfit for the trial
	6. CHARM (a) those who have ever used HXZQ for treating eczema (b) medication used: systemic therapy with immunomodulatory or immunosuppressive agents (including tripterygium wilfordii) within the previous 4 weeks; topical or systematic therapy with antibiotics or antihistamines within the previous 2 weeks phototherapy (such as PUVA, UVA, or UVB) within the previous 4 weeks; topical therapy with immunomodulator within the previous 2 weeks; or topical or systematic use of any over-the-counter drugs within the previous week (c) those who are participating in any other clinical trial or had participated in a clinical trial within the previous month

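### The dampness versus nondampness contrasts (3) to (5) are presented as evidence on the HXZQ effect, but pattern is confounded with treatment setting and eligibility, so they cannot supply it

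*Protocol article*

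**What the plan says.** Section 2.8.2 ends with a combined analysis: "an overall analysis will be performed combining multiple subgroups to comprehensively investigate the effect of HXZQ for dampness pattern". It lists five comparisons. Comparisons (1) and (2) are HXZQ against placebo in AD and in IBS-D. The other three set dampness against nondampness: the first of them reads "3) AD patients with dampness pattern vs. AD patients without dampness pattern", the next does the same within IBS-D, and the last pools both diseases. The Discussion names dampness versus nondampness among the comparisons that fill out the efficacy profile of HXZQ, and adds that efficacy will be analysed between pattern groups. The Introduction describes the whole design, trials plus observational study, as undertaken "with the aim of identifying the accurate pattern-defined population of HXZQ".

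Pattern decides the substudy (2.2 and 2.3.1): dampness leads to a trial, nondampness to the observational study. On the observational side, 2.4.3 says "In the observational study part, patients will receive no experimental interventions of this study", and 2.4.2 says "Treatments in the observational study will be provided by clinicians". On the trial side, 2.4.2 prohibits other effective treatment apart from recorded rescue. Table 2 adds a further screen, for example "1% < body surface area (BSA) < 10"% and IGA 1 to 3 for AD, and IBS-SSS above 75 with anxiety and depression cut-offs for IBS-D. The cohort criteria in 2.3.2 and 2.3.3 contain no severity limits.

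**The concern.** To learn whether HXZQ acts differently in dampness, one needs HXZQ against a control in both patterns. This design has that comparison in dampness only. Contrasts (3) to (5) therefore set trial patients on HXZQ or placebo, with restricted background care, against a less selected group on open usual care. A difference could be read as an HXZQ or pattern effect when it comes from usual care or selection. A null result could equally hide a real HXZQ effect. What is at stake is the interpretation of the combined analysis, and in particular any statement that HXZQ suits dampness patients better than others.

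**Working it through.** **Inputs.** Trial sizes: 218 AD and 212 IBS-D, total 430 (2.8.1, Table 1). Nondampness sizes: 460 AD and 110 IBS-D, total 570 (Table 1). Assumed dampness prevalence: 39% and 81%; loss to follow-up 15% (2.8.1). Allocation 1:1 (2.2).

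**The plan's own figures.** 218/0.39 = 559 (stated 560) and 212/0.81 = 262 (stated 270). After loss, 560/0.85 = 659 (stated 678), 270/0.85 = 318 (stated 322) and 830/0.85 = 977 (stated 1000). All agree to within about 3%. The nondampness counts are exact: 678 − 218 = 460, 322 − 212 = 110, sum 570. The sizes are not in dispute.

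**What a contrast estimates.** Let P be the effect of pattern, H the effect of HXZQ over placebo in dampness patients, U the effect of usual care over the restricted trial background, and S the difference due to selection. The expected dampness minus nondampness difference is:

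- both trial arms pooled: P + H/2 − U + S
- HXZQ arm only: P + H − U + S
- placebo arm only: P − U + S

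The article does not say which version is meant. In none of them can P be separated from U and S.

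**Effect modification.** Code D = 1 for dampness and H = 1 for assigned HXZQ. Assigned HXZQ occurs only where D = 1 (0 of 570 nondampness patients), so the product D×H is identical to H. The design matrix with intercept, D, H and D×H has rank 3 of 4 in AD, in IBS-D and pooled. Adding a usual-care column, which as designed equals 1 − D, gives rank 3 of 5. The pattern-by-HXZQ interaction is not estimable, whatever the sample size.

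**Illustration (assumed values, not in the documents).** Adequate-relief scale, P = 0, S = 0, arms pooled, so the contrast is H/2 − U:

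| U | H = 0 | H = 0.20 |
|---|---|---|
| 0 | 0 | +0.10 |
| 0.10 | −0.10 | 0 |
| 0.20 | −0.20 | −0.10 |
| 0.30 | −0.30 | −0.20 |

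A contrast of zero fits both a useless HXZQ and one with a 20-point effect. In IBS-D (212 versus 110), with an assumed responder rate of 0.40 in the trial patients, H = 0 and P = 0, the chance of p < 0.05 is about 0.40, 0.93 and above 0.99 for U = 0.10, 0.20 and 0.30.

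**Contrast (5).** AD share among dampness patients: 218/430 = 51%. Among nondampness patients: 460/570 = 81%. On any responder scale common to both diseases, with rates a (AD) and b (IBS-D) unaffected by pattern or treatment, the pooled difference is (0.507 − 0.807)(a − b) = −0.30(a − b). If a and b differ by an assumed 0.20, disease mix alone produces 0.06. The two primary outcomes also differ (2.5.1).

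**The case against.** The strongest reply is that little depends on these contrasts. The primary objective in 2.1 is efficacy and safety in dampness patients within each disease. The randomized contrasts answer it, and each trial is analysed on its own first. Contrasts (3) to (5) also fit secondary objective (2), on how outcomes relate to pattern. All of this stands.

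A reader might infer that the aim of finding a pattern-defined population rests on (3) to (5). The documents do not support that: the Discussion ties this aim to analysis of pattern changes within the two trials. Nor does 2.1 claim a benefit relative to nondampness. What remains is that 2.8.2 and the Discussion present the contrasts as evidence on HXZQ. The trials, which enrol dampness patients only, cannot fill the gap.

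A second reply is that HXZQ is sold over the counter and usual care is open, so some nondampness patients may take it. The zero applies to assignment, not necessarily to exposure. Likewise, coding usual care as 1 − D describes the design and does not measure the care actually received. However, no nondampness HXZQ group is planned, and any such users would be self-selected and unblinded.

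A third reply is that arm choice, time points and covariates belong to the analysis plan. That is fair, and their absence is not criticised here. The problem is the purpose that the protocol itself assigns to the contrasts. The challenges listed in the Discussion cover uncertain pattern classification and differing outcomes, but not this confounding.

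**Conclusion.** The point holds as a limit on what contrasts (3) to (5) can show. They estimate neither the HXZQ effect nor its modification by dampness status, because pattern determines both treatment setting and eligibility and no nondampness patient is assigned HXZQ. This follows from the design as written and needs no assumed figure; the responder-rate examples show direction and possible size only.

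Two stronger readings should be avoided. One is that the imbalance can be expressed in EASI points: the documents give no baseline EASI for either group, and the Discussion proposes EASI-50 and EASI-75, which are relative measures, for comparing subpopulations. The other is that using the placebo arm with adjustment would rescue the comparison: placebo with restricted background care would still face open usual care. The randomized comparisons, the sample sizes and the primary objective are unaffected. The correction matters because it changes what the combined analysis may conclude.

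**What to change.** In 2.8.2 and the Discussion:

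- Draw conclusions on the HXZQ effect only from contrasts (1) and (2).
- Label (3) to (5) as descriptive or prognostic, serving secondary objective (2).
- State that the design cannot show HXZQ benefit in dampness relative to nondampness.
- Pursue the pattern-defined population inside the trials, as the Discussion already indicates, through interactions of treatment with baseline pattern features. These speak only to features among dampness patients.
- For the descriptive contrasts, report the trial arms separately and by disease, at the shared weeks 4 and 8. Adjust for the baseline severity that Table 3 already collects in both parts (EASI, BSA and IGA; IBS-SSS). This reduces the selection difference but does not remove the confounding with usual care, so the relabelling is needed in any case.

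The cost is a more modest claim and a little more analysis. No new patients or measurements are needed.

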## 3. Discussion

This master protocol was designed to evaluate the Chinese herbal formula HXZQ as a common dampness-resolving therapy for both AD and IBS-D patients. Combining the RCT and observational study design, this study can depict a more comprehensive efficacy profile of HXZQ through multiple subgroup comparisons, for example, patients with AD vs. patients with IBS-D, and patients with dampness pattern vs. patients without dampness pattern. Besides, the analysis of CM pattern changes in the two RCTs may enable us to identify the pattern-defined population of HXZQ that is with the best therapeutic effect. To our knowledge, a master protocol design has not been used to conduct efficacy research of HXZQ concurrently in multiple diseases, and its use will increase efficiencies in study design, participant enrollment, and data collection.

A master protocol is designed to answer several research questions within the same overall trial structure [21]. The general idea of the master protocol is to provide a platform for simultaneously evaluating multiple interventions [37]. It may involve one or more interventions in multiple diseases, or a single disease with multiple interventions [22]. This design concept is compatible with the flexibility of treatment based on pattern differentiation. In particular, when master protocol defines substudies based on CM pattern to investigate a common pattern-resolving therapy in different diseases, it is highly consistent with the CM therapeutic principle of “treating different diseases with the same therapy” [38]. Hence, master protocol design may facilitate the development of efficacy evaluation methods in CM. At present, there is also a growing interest in performing master protocol to study the efficacy of CM [39, 40].

In addition, different from previous studies that evaluate CM efficacy mainly on a disease basis, namely, disease dominating CM pattern research model (Yi Bing Tong Zheng model), we conduct this overarching trial from a pattern perspective. Participants are grouped by different CM patterns to enter either the RCTs or the observational study. The efficacy analysis will also be performed between different CM pattern groups. Importantly, the changes of CM pattern over time as well as the correlation of CM patterns and disease outcomes will be explored using multiple methods. Such a strategy is defined as CM pattern dominating different diseases (Yi Zheng Tong Bing model), closely reflecting the idea of “treating different diseases with the same therapy.” Compared with disease dominating pattern, the mainstream model in CM research, pattern dominating disease takes CM pattern as the target of intervention and evaluation, providing a parallel model for CM efficacy studies [24, 39]. To date, this model is still under development, and many efforts are needed to establish a feasible research framework, so it is also our hope that the resulting procedure in this study can provide a reference for future studies.

It should be mentioned that this study faces several challenges. First, the master protocol design increases coordination to bring all the stakeholders into agreement on trial design, conduct, and governance and adds to the difficulty of trial management as well as data analysis [22, 37]. To manage these complexities, we have had intensive pretrial discussions among sponsor and investigators to develop a more reasonable overall plan. Experts in the field have been invited to help with the study design and statistical analysis, and an independent DSMB was established to monitor the conduct of the study. Second, the classification of dampness pattern and nondampness pattern may be challenging. CM pattern differentiation is a fundamental procedure in our study determining which substudy a patient can be enrolled in. However, no reliable and accurate diagnostic criteria for dampness pattern have been developed, so the accuracy of pattern classification remains controversial. In response to this problem, we have conducted a literature survey to find a relatively credible standard and invited clinical experts to discuss and define a final criterion. Moreover, investigators were required to receive a training on criterion application. Third, the primary outcome is different in AD and IBS-D, making it difficult to directly compare the therapeutic effect on dampness pattern among multiple subpopulations. In general, the master protocol is designed on the basis of a common denominator, and its substudies often adopt the same outcome measurement to achieve efficacy comparability. Due to the lack of consistent criteria for efficacy evaluation on CM pattern [41, 42], we still choose the commonly recommended EASI score and AR responder proportion as the primary outcome [29, 30, 43]. The secondary outcomes of AD in our study include EASI-50 and EASI-75, which refer to an EASI score showing improvement exceeding 50% and 75%, respectively. To some extent, these two measurements have a similar explanatory effect to AR responder proportion, so the analysis and comparison of different subpopulations data could also be performed. Besides, other common outcome measurements such as EQ-5D-5L may also facilitate the comparison.

In conclusion, this study will provide high-quality efficacy evidence of HXZQ for AD and IBS-D patients and give an example of postmarketing evaluation for CM products under the pattern dominating different diseases research model.

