### 2.5. Outcome Measurements

#### 2.5.1. Primary Outcome

For all AD patients, the primary outcome is the change in the Eczema Area and Severity Index (EASI) scores from baseline to the end of treatment (4^th^ week). EASI is the core outcome measurement instrument for AD, and the higher the score is, the more severe the AD is [29]. For IBS-D patients, the proportion of responders for adequate relief (AR) is the primary outcome evaluating the degree of symptom alleviation [30]. Throughout the study, IBS-D patients will be weekly asked the question: “Has your irritable bowel syndrome pain and discomfort adequately relieved in the past week?” (yes/no). Responders are defined as those who answer “yes” for at least 50% of the time, for example, in the RCT, that is, 2 out of 4 weeks in the treatment period. The proportion will be separately analyzed in the treatment period and the follow-up period.

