#### 2.5.2. Secondary Outcomes

The secondary outcomes for AD include numerical rating scale (NRS) in the pruritus, investigator's global assessment (IGA) scale, body surface area (BSA), Skindex-29 (a dermatology-specific quality of life instrument), EuroQol-5-Dimensions-5-Level (EQ-5D-5L), antihistamine use, and CM pattern. Besides, EASI-50 and EASI-75 will be assessed, which refer to an EASI score showing improvement exceeding 50% or 75% during the treatment period, respectively [25]. For IBS-D patients, secondary outcomes are the Irritable Bowel Syndromes Symptom Severity Score (IBS-SSS), the Irritable Bowel Syndrome-Quality of Life Questionnaire (IBS-QOL), EQ-5D-5L, CM pattern manifestations [26].

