	7. CHAIRS (a) Patients with warning signs (weight loss within 3 months of emaciation >10%), hematochezia that is confirmed not to have been caused by hemorrhoids or anal fissure, diarrhea at night, fever, family history of colorectal cancer (or polyposis syndrome), inflammatory bowel disease (IBD) or celiac disease (b) Organic diseases of the digestive system, or systemic diseases that affect digestive tract dynamics (c) Patients with a history of abdominal surgery (except caesarean section) (d) Those who are unwilling or unable to stop using drugs that affect the evaluation of interventions during the study (e) Standard points on the self-rating anxiety scale (SAS) > 50; standard points on the self-rating depression scale (SDS) > 53 (f) Those who have participated in other trials within the past 3 months

CHARM, Chinese herbal formula Huoxiang Zhengqi for atopic dermatitis with dampness pattern; CHAIRS, Chinese herbal formula Huoxiang Zhengqi for diarrhea-predominant irritable bowel syndrome; CM, Chinese Medicine.

**Table 3 tab3:** Study schedule.

		RCTs				Observational studies			
		Baseline	Treatment period		Follow-up	Baseline	Follow-up		
		0 week	2^nd^ week (AD only)	4^th^ week	8^th^ week	0 week	4^th^ week	8^th^ week	12^th^ week
Patient	Informed consent	×				×			
	Demographics	×				×			
	Medical history	×				×			
	Clinical manifestations	×		×	×	×	×	×	×
	CM pattern differentiation	×		×	×	×	×	×	×

Interventions	Randomization	×							
	HXZQ or placebo								
	Medical record					×	×	×	×
	Concomitant medications		×	×	×				

Outcome measurements									
AD patients (only)	EASI	×	×	×	×	×	×	×	×
	BSA	×	×	×	×	×	×	×	×
	NRS、 IGA	×	×	×	×	×	×	×	×
	Skindex-29、EQ-5L-5D	×	×	×	×	×	×	×	×
	EASI-50、EASI-75		×	×	×		×	×	×
IBS-Dpatients (only)	Adequate relieve								
	IBS-SSS	×		×	×	×	×	×	×
	IBS-QOL	×		×	×	×	×	×	×
	EQ-5D-5L	×		×	×	×	×	×	×

Safety assessment	Vital signs	×		×	×	×	×	×	×
	Laboratory tests and ECG	×		×		×			
	Adverse events		×	×	×		×	×	×

EASI, Eczema area and severity index; BSA, body surface area; NRS, numerical rating scale; IGA, investigator's global assessment; Skindex-29, a dermatology-specific quality of life instrument; EQ-5D-5L, euroQol-5-dimensions-5-level; IBS-SSS, irritable bowel syndromes symptom severity score; IBS-QOL, the irritable bowel syndrome-quality of life questionnaire.

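### EASI-50/75 and the adequate-relief responder rate are not similar enough to support AD versus IBS-D or pooled responder comparisons; use a measure common to both diseases

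*Protocol article*

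**What the plan says.** **The bridge (section 3, Discussion).** The article lists as a challenge that "the primary outcome is different in AD and IBS-D, making it difficult to directly compare the therapeutic effect on dampness pattern among multiple subpopulations". It then says of EASI-50 and EASI-75 that, to some extent, "these two measurements have a similar explanatory effect to AR responder proportion", and concludes that data from different subpopulations could be analysed and compared. The next sentence adds EQ-5D-5L as a common measure. Earlier in the Discussion, the comparisons meant to fill out the efficacy profile of HXZQ include "patients with AD vs. patients with IBS-D".

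**The definitions.**
- EASI-50/75 (2.5.2): these "refer to an EASI score showing improvement exceeding 50% or 75% during the treatment period, respectively".
- AR (2.5.1): patients are asked weekly whether pain and discomfort were adequately relieved. "Responders are defined as those who answer “yes” for at least 50% of the time", which the article illustrates as 2 of the 4 treatment weeks.

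**The schedule (Table 3).** The row "EASI-50、EASI-75" is marked at RCT weeks 2, 4 and 8 and at observational weeks 4, 8 and 12.

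**The planned overall analysis (2.8.2).** Five contrasts are listed. Number (5) pools both diseases and compares patients with and without dampness pattern. Its outcome is not named. A separate AD versus IBS-D comparison is planned on change in dampness pattern.

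**The concern.** The claimed similarity is the stated reason why subpopulations with different primary outcomes can be compared, and no argument or citation supports it. If the two responder rates are set side by side, or merged into one responder outcome for contrast (5), part of any difference will come from how easily each instrument yields a responder. That part would be read as a difference between diseases, or between pattern groups, in benefit from HXZQ. Comparison across diseases is a main reason for using a master protocol here, so the basis for it should be sound.

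**Working it through.** **1. The two definitions side by side**

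| | EASI-50/75 | AR responder |
|---|---|---|
| What is measured | Skin severity score | Yes/no on relief of pain and discomfort |
| Baseline | Relative improvement in the score | No baseline value |
| Time | Scheduled visits | Weekly answers over a period |
| Meaning of 50% | Fall in score | Share of weeks |
| Cut | Must exceed it | Reaching it is enough |

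An IBS-D patient with relief in weeks 1 and 2 and none in weeks 3 and 4 is an AR responder. EASI-50 read at week 4 has no counterpart to that.

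The time window alone shifts the rate. With weekly response probability p and independent weeks (an assumption), P(at least 2 of 4) = 1 − (1−p)⁴ − 4p(1−p)³. For p = 0.40 this is 1 − 0.1296 − 0.3456 = 0.525, against 0.40 at a single visit. For p = 0.20 it is 0.18, and for p = 0.60 it is 0.82. With perfectly correlated weeks the shift vanishes.

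**2. Effect on pooled contrast (5)**

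Inputs from Table 1: dampness 218 AD and 212 IBS-D (430); nondampness 460 AD and 110 IBS-D (570). Assumed: EASI-50 20% and AR 40% in everyone, with no drug or pattern effect.

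- Dampness: (218×0.20 + 212×0.40)/430 = 128.4/430 = 29.9%
- Nondampness: (460×0.20 + 110×0.40)/570 = 136/570 = 23.9%
- Spurious gap: 6.0 points

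In general the gap is (AR rate − EASI rate) × (212/430 − 110/570) = (AR rate − EASI rate) × 0.300. With AR at 40%, an EASI-50 rate of 10% gives 9 points, 30% gives 3 points, and 40% gives none. Within each disease the gap is zero throughout.

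**3. Effect on an AD versus IBS-D comparison**

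Arm sizes at 1:1 are 218/2 = 109 and 212/2 = 106; two-sided alpha is 0.05 (2.8.2). The drug effect is assumed equal in both diseases: a shift d on a latent normal scale, so p₁ = Φ(Φ⁻¹(p₀) + d). The AR placebo rate is assumed to be 40%. The table gives the chance of a significant disease difference.

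| EASI-50/75 placebo rate | HXZQ arms compared directly, d = 0 | HXZQ arms compared directly, d = 0.4 | Placebo-controlled risk differences compared, d = 0.4 |
|---|---|---|---|
| 5% | about 100% | about 100% | 26% |
| 10% | about 100% | about 100% | 13% |
| 20% | 90% | 93% | 6% |
| 30% | 34% | 35% | 5% |
| 40% | 5% (2.5% per tail) | 5% (2.5% per tail) | 5% |

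Worked case for the 20% row, last column:
- p₁ is 0.329 in AD and 0.558 in IBS-D, so the risk differences are 0.129 and 0.158, which differ by 0.029.
- SE = √(0.329×0.671/109 + 0.20×0.80/109 + 0.558×0.442/106 + 0.40×0.60/106) = 0.090, so z = 0.32.
- Rejection probability = Φ(0.32 − 1.96) + Φ(−0.32 − 1.96) = 0.062.

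With d = 0 the placebo-controlled comparison rejects 5% of the time in every row.

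**4. Definition against schedule**

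Section 2.5.2 ties EASI-50/75 to the treatment period. Table 3 also schedules it at RCT week 8, after treatment ends, and at observational weeks 4 to 12, where no study treatment is given. The Discussion repeats the definition without the treatment-period limit.

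**The case against.** The strongest reply is that this is a disclosed limitation with a hedged workaround. The article calls direct comparison difficult, says only that the measures are similar to some extent, and offers EQ-5D-5L itself. None of the five contrasts in 2.8.2 tests EASI-50/75 against AR, and the AD versus IBS-D comparison planned there uses dampness pattern change, which is recorded in both diseases. All of this stands, and it limits the point. The hedged sentence still concludes that comparison can proceed, and contrast (5) leaves its outcome open.

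A reader might infer more than the documents support:

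- **That the measures are declared equivalent.** They are not.
- **That a false disease difference is certain or large.** Assuming placebo rates of 20% and 40% and a common odds ratio of 1.8, the HXZQ arms would show 31.0% and 54.5%, a gap of 23.5 points. That needs the HXZQ arms to be compared across diseases without placebo, which the article does not propose. The placebo-controlled differences are 11.0 and 14.5 points, and at similar rates the false-positive rate in the table above is about 6%.
- **That the assessors differ.** AR is answered by the patient, but the article does not say who rates EASI.
- **That the strict cut for EASI-50/75 matters numerically.** The article gives no EASI distribution from which to size the share of patients exactly on the cut.

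**Conclusion.** The point holds in a limited form. By the article's own definitions the two responder measures differ in construct and time window, and their 50% thresholds mean different things, so the asserted similarity is not a valid basis for comparing or pooling across diseases. Doing so can produce a difference from instruments or disease mix alone: 6 points in contrast (5) under the assumed 20% and 40% rates, and 3 to 9 points over EASI-50 rates of 30% to 10%. All response rates and the latent effect are assumptions. The bias is small for placebo-controlled contrasts when background rates are close and absent when they are equal. Neither primary outcome, neither sample size and neither within-disease HXZQ versus placebo result is affected. The mismatch between the EASI-50/75 definition and Table 3 is a separate inconsistency and stands whatever the background rates. This is a cheap improvement worth making, not a threat to the trials' main conclusions.

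**What to change.** 1. Withdraw the statement that EASI-50/75 can stand in for the AR responder proportion.
2. Base any AD versus IBS-D efficacy comparison on a measure recorded in both diseases: EQ-5D-5L, which Table 3 schedules in both RCTs at weeks 0, 4 and 8, or the CM pattern change already planned in 2.8.2. Estimate HXZQ minus placebo at week 4 within each disease, test the treatment-by-disease interaction, and label the result exploratory.
3. Name the outcome for contrast (5) and stratify it by disease. This removes the disease-mix artefact only; other differences between trial and observational patients remain.
4. Define EASI-50/75 as change from baseline at each named visit, with week 4 as the treatment-period result, so that 2.5.2, the Discussion and Table 3 agree.

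The cost is wording in the protocol and SAP, with no new data. The downside is precision: EQ-5D-5L may be insensitive in mild disease, so the cross-disease estimate will be imprecise. CM pattern has its own limit as a common measure, because its criteria (2.3.4) include a disease-specific route.
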